### Confidentiality {33}

All of the materials collected are for research purposes only, and data will be kept in strict confidence. Confidentiality will be ensured by the use of identification codes. All data collected will be identified with an alphanumeric identification code unique to the participant. Records that link each participant to their identifier will be kept locked in secure computer files at the sites coordinating data collection (GSU, Emory, and Grady), and only the PI and the project manager will have access to the list of identifiers.

## Statistical methods

### Statistical methods for primary and secondary outcomes {27a}

We will conduct intent-to-treat analysis. All participants who were originally assigned to different treatment conditions are analyzed as part of their original conditions, regardless of whether they completed the treatment or adhered to the protocol. Analyses will be performed using SAS or R software. All statistical tests will be two-tailed (*α* = 0.05). The treatment condition will be compared to the control condition; if significant differences are observed (*p* < 0.05), the results will be interpreted as evidence of treatment effect.

Descriptive statistics for all measurements will be reported separately for each trial (people who smoke with SPD, with low SES, and with neither). Frequency distributions will summarize categorical data, and measures of central tendency and dispersion will summarize continuous data. All data will be examined for bivariate relationships with the outcomes and with each other.

For each trial, the primary analysis will be regression models to test the difference in the mean CPD (cigarettes smoked per day) between those in the treatment condition and those in the control condition, adjusting for the baseline CPD value and other covariates that are strongly correlated with the outcome (*r* ≥ 0.3) [49]. Analyses of secondary outcomes will be similar to the analysis of the primary outcome. We will use multivariable regression models to examine differences between the treatment and the control arm while accounting for potential covariables.

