### Randomization, intervention and weekly visits

During the randomization visit (1 week after baseline), participants will be randomized into treatment (VLNCs + messages) or control (VLNCs only). Participants will be randomized using a 1:1 ratio into treatment (VLNCs + messages) or control (VLNCs only). We will use simple randomization with stratification by site, readiness to quit (planning to quit in the next 6 months vs. not), and menthol preference (menthol vs. non-menthol) with no required sample size for any of these strata. During the randomization and weekly visits, participants will complete questionnaires and provide an expired CO sample. At each visit, they will receive a 14-day supply of VLNCs (with or without the inserts, according to the assigned condition). This will ensure adequate availability of cigarettes in the different locations where participants may typically keep a supply (home, work, vehicle, etc.) as well as avoid expending the entire supply if they miss a scheduled visit. They will be instructed to return all unused cigarettes and empty cigarette packs each week; empty packs will be saved, and unused packs will be redistributed to the participants during subsequent visits. At each visit, they will see 4 messages about VLNCs (in the treatment condition) or, in the control condition, no messages. At each visit, participants will be counseled about daily log completion (based on staff review of compliance during the prior week), visit attendance, and returning unused cigarettes. Throughout the 4 weeks of the study, participants will continue to complete daily logs. During the last visit (end of week 4), participants will be referred to smokefree.gov and given a Quitline number.

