### Daily logs

From the baseline period through week 4, daily logs will be collected via text messages (sent via Twilio) with links to brief online surveys in REDCap. Daily logs will assess their use of study and non-study cigarettes and other combusted and non-combusted tobacco products. Participants will report tobacco use in the past day.

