#### Assignment of interventions: randomization

### Sequence generation: who will generate the sequence {21a}

During the randomization visit (after 1-week baseline), a separate computer-generated allocation sequence will be created for participants at each site using stratified randomization to ensure balance across conditions.

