### Sequence generation: type of randomisation {21b}

Participates will be stratified by readiness to quit (planning to quit in the next 6 months vs. not) and menthol preference (menthol vs. non-menthol). Within each stratum, participants will be randomized in a 1:1 ratio to either the treatment (VLNCs + messages) or the control (VLNCs only) condition.

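### The primary model leaves the randomization factors to a data-driven r ≥ 0.3 rule, which costs some precision and leaves the covariate set unfixed until outcomes are examined

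*Protocol article*

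**What the plan says.** For each of the three populations, section {27a} of the protocol article compares mean CPD between arms by regression, "adjusting for the baseline CPD value and other covariates that are strongly correlated with the outcome"; the same sentence sets the cut-off at r ≥ 0.3. The paragraph before it announces that "All data will be examined for bivariate relationships with the outcomes and with each other". For secondary outcomes the models are described only as comparing the arms "while accounting for potential covariables". No list of candidate covariates is given, and nothing expressly limits them to variables measured before randomization.

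On allocation, the section *Randomization, intervention and weekly visits* says "We will use simple randomization with stratification by site, readiness to quit", and names as the third factor "menthol preference (menthol vs. non-menthol) with no required sample size for any of these strata". Section {21a} describes per-site sequences "using stratified randomization to ensure balance across conditions". Section {21b} repeats the other two factors: "Participates will be stratified by readiness to quit". No section says that these factors belong in the analysis model.

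**The concern.** Factors thought important enough to stratify on are normally in the primary model by design. Here they must earn their place by an observed correlation with the outcome, at a level a binary factor seldom reaches. If they are prognostic but fall short of the cut-off, the treatment estimate carries variance that could have been removed at no cost. The trial expects messaging effects to be small at most, so lost precision matters.

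The second issue is prespecification. The rule is applied separately in three populations, each with its own primary analysis. Nobody can write down any of the three models today, and they may differ for no reason other than sampling variation around 0.3. In an open-label trial, that invites questions that a fixed model would avoid.

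**Working it through.** **Sample size, as stated in section {19}.** 262 / 0.8 = 327.5, rounded up to 328 randomized; 328 / 0.8 = 410 enrolled; 3 × 410 = 1,230. The plan's figures reproduce, and the check below uses n = 262 completers per population.

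**Step 1: how often would a stratification factor pass the rule?** By Fisher's z, and reading the rule as an absolute correlation, P(sample r ≥ 0.3) = 1 − Φ[(atanh 0.3 − atanh ρ) × √(n − 3)]. For ρ = 0.20: (0.3095 − 0.2027) × √259 = 1.72, so P = 0.04.

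| True r | P(enters), n = 262 | P(enters), n = 328 |
|---|---|---|
| 0.10 | 0.00 | 0.00 |
| 0.20 | 0.04 | 0.03 |
| 0.25 | 0.19 | 0.17 |
| 0.30 | 0.50 | 0.50 |
| 0.35 | 0.82 | 0.84 |

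For a factor split 50/50, r = 0.3 corresponds to a difference of 2 × 0.3 / √(1 − 0.09) = 0.63 SD between its levels.

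**Step 2: what does leaving the strata out cost?** Assumptions, none given in the document: baseline CPD correlates 0.6 with the outcome; each of the three factors correlates s with it; the factors are independent of baseline CPD and of each other. Residual variance is 1 − 0.36 without the strata and 1 − 0.36 − 3s² with them. The inflation is the ratio of the two, and power is Φ(2.80/√inflation − 1.96), starting from 80% with the strata in.

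| s | Variance inflation | Equivalent completers of 262 | Power |
|---|---|---|---|
| 0.10 | 0.64/0.61 = 1.05 | 250 | 78% |
| 0.15 | 0.64/0.5725 = 1.12 | 234 | 75.5% |
| 0.20 | 0.64/0.52 = 1.23 | 213 | 71% |

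Varying the baseline correlation from 0.5 to 0.7 gives 1.04 to 1.06 at s = 0.10 and 1.19 to 1.31 at s = 0.20.

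**Step 3: does the rule distort the type I error?** Null simulation, n = 262, 6,000 runs per setting, s = 0.10, 0.20 and 0.25, with two further covariates at true r = 0.3.

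- Simple assignment within strata: the rule rejects in 4.8% to 5.3% of runs, which is nominal.
- Assignment blocked within strata: the rule rejects in 4.6%, 2.6% and 2.6%. The model with baseline CPD and strata rejects in 4.8% to 5.6%.

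There is no inflation. The test is conservative only when allocation really balances the strata.

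**Step 4: would the three trials share a model?** In the same simulation, three independent trials selected the same covariate set only about 1% to 6% of the time.

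**A limit on step 2.** It compares models that differ only in the strata. In the simulation at s = 0.10, under simple assignment, the rule had a smaller mean standard error (0.0906) than baseline CPD plus strata (0.0974), because it often picked up the two further covariates. At s = 0.20 the two were equal to three decimals (0.0899 and 0.0900), and at s = 0.25 the strata model was better (0.0839 against 0.0863). The rule is thus not always the less precise choice. What it gives away is the variance explained by the strata, and a fixed model can include other strong baseline covariates as well.

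**The case against.** The strongest reply is that the omission is conditional and may cost little. A factor that reaches r ≥ 0.3 enters, and nothing bars the strata. At r near 0.10 the power loss is about two percentage points. The protocol treats the three populations as distinct trials, so different models are not in themselves an error. A statistical analysis plan may also settle the covariates. The first three points stand as limits on size. The last does not remove the concern, because the protocol is not silent: it states a rule, and the rule would have to be overridden.

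A reader might infer more than the text supports:

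- *That screening on the outcome inflates the false-positive rate.* The correlations can be computed on pooled data without arm labels, the text does not say that arm is used, and step 3 shows no inflation.
- *That the standard error will be too wide.* That requires restricted allocation that truly balances the arms within strata. The words "We will use simple randomization with stratification by site, readiness to quit" do not establish it, no block scheme is mentioned, and balance in section {21a} is a purpose rather than a mechanism.
- *That on-treatment measures such as carbon monoxide or dependence will be adjusted for.* The sentence on screening all data belongs to the descriptive paragraph, and Table 2 lists those measures as outcomes. Their use is not excluded, but it is not stated either.
- *That the source of baseline CPD is a defect.* CPD is recorded at the baseline visit, and also in logs: "From the baseline period through week 4, daily logs will be collected via text messages". Choosing between the two is ordinary detail for the analysis plan.

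**Conclusion.** The concern holds in a limited form. The stated rule leaves the three randomization factors to a threshold that moderately prognostic factors rarely reach, and it leaves the primary model in each trial unknown until outcome data are examined. The harm is to precision and prespecification; validity of the test is not at stake.

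The rarity of passing the threshold follows from the rule and the planned 262 completers. The size of the precision loss rests on assumed correlations: small if the strata are weakly prognostic, material if each has r near 0.20. The document does not say which applies. The case for changing the plan does not depend on the answer, since fixing the model costs next to nothing in either case.

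**What to change.** Prespecify the primary model in each of the three trials as arm + baseline CPD + site + readiness to quit + menthol preference. Any other pre-randomization covariates judged prognostic should be named and fixed before outcome data are examined. Replace the r ≥ 0.3 rule, or keep it only as a sensitivity analysis. State that only pre-randomization variables may be used for adjustment in a treatment-effect model. For secondary outcomes, use the same strata plus the baseline value of the outcome where it is collected.

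The cost is analysis wording. The variables are already collected for stratification and at baseline, the three added terms take few degrees of freedom with 262 completers, and the sample size does not change. Recruitment began in September 2025 and data collection is expected to run to January 2029, so the change can be made well before the final analysis; it should also precede any interim analysis under section {28b}.

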Date of First Enrollment	First enrollment began 11 September 2025
Sample Size	1,230
Primary outcome(s)	Cigarettes smoked per day
Key Secondary outcome(s)	Use of other tobacco products; Use of nicotine replacement therapy; Perceived risks of smoking VLNCs; Quit intention; Nicotine dependence; Forgoing cigarette behaviors.
Ethics Review	This study was approved by the GSU institutional review board (protocol H25318).
Individual Trial Participant Data sharing statement	All study data will be deposited in the ScholarWorks@Georgia State University institutional repository within 1 year of study completion. The compiled dataset will be publicly accessible through the ScholarWorks@Georgia State University website. Users seeking access must adhere to specific conditions as specified by the ScholarWorks. Redistribution of the data to third parties will not be permitted.

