#### ***Hypotheses***

With the primary aim of testing the effect of messages about VLNCs accompanied with VLNC use (vs. use of VLNCs without messages) on the number of cigarettes smoked per day, we hypothesize that participants exposed to messages in combination with VLNC use will smoke fewer study and non-study cigarettes per day compared to those using VLNCs without receiving any messages.

The second aim is to examine the effect of messages about VLNCs in combination with VLNC use (vs. use of VLNCs without messages) on the use of other tobacco products (e.g., cigarillos, e-cigarettes), cigarette dependence, and cessation-related outcomes over the study period. We hypothesize that exposure to messages in combination with VLNC use will lead to (1) less non-study cigarette use, (2) less cigarette dependence, and (3) an increase in the forgoing of cigarette behaviors compared to VLNCs without messages. The third aim is to examine the effect of messages about VLNCs in combination with VLNC use (vs. use of VLNCs without messages) on perceptions and behavioral intentions. We hypothesize that exposure to messages in combination with VLNC use will lead to (1) increased perceived risk of smoking VLNCs, (2) increased self-efficacy to quit smoking, and (3) increased intention to quit or cut down smoking compared to VLNCs without messages.

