### Sample size {19}

In the randomized clinical trial, participants will be randomized into one of two conditions: treatment (VLNCs with messages) or control (VLNCs only). We will conduct three separate trials, each targeting a specific group of people who smoke: (1) individuals with serious psychological distress (SPD), (2) individuals with low SES (defined as having a high school education or less or with household income less than 200% of the federal poverty level), and (3) individuals who are neither of those two groups. For each group, we will have 262 participants to complete the 4-week study. This number accounts for a 20% attrition during the 1-week baseline and an additional 20% attrition during the study period; thus, we will enroll 410 participants and randomize 328 participants to achieve 262 completes for each smoker group. The projected attrition rates are conservative and are based on our own studies and past RCTs with VLNCs [39–41], including with the same priority populations (e.g., 24% attrition during an intensive 8-week study that used ecological momentary assessments in the similar populations in Atlanta, GA [42]; 18% attrition for a 12-week study with smokers with low SES and mental health conditions [13]).

Based on the above assumptions and adjusting for missing data (0–20%) in daily logs, with 262 participants in each participant group completing our study, we will be able to detect the following effect sizes. For data collected in daily logs (28 observations per person): primary outcome (cigarettes per day) and secondary outcomes (use of other tobacco products, cessation medications, and foregoing cigarettes), the study has sufficient (0.80) power to detect small effect sizes (*d* = 0.11–0.17, depending on the level of autocorrelations and missing data). For data collected in weekly in-person visits (5 observations per person): secondary outcomes related to cessation behaviors, perceptions, and physiological responses, the study has sufficient power to detect small-to-medium effect sizes (*d* = 0.27–0.38, depending on the level of autocorrelations and missing data). Cohen’s definition of effect sizes will be used (small *d* = 0.20, medium *d* = 0.50, large *d* = 0.80 [43, 44]).

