### Who will be included in each analysis {27b}

Following an intent-to-treat principle, all randomized participants will be analyzed in the trial condition to which they were originally assigned (VLNCs and messages vs. VLNCs only), regardless of adherence, exposure to messages, product use, or study discontinuation. Primary and secondary outcomes will be analyzed separately within each of the three groups (participants with SPD, low SES, and neither) so that each participant contributes only to the analysis group corresponding to the population in which they were enrolled.

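### The rule that p < 0.05 is evidence of a treatment effect is not limited to cigarettes per day, so it also covers every secondary outcome in each of the three populations

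*Protocol article*

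**What the plan says.** Section {27a} of the protocol article covers primary and secondary outcomes together. Its first paragraph sets the level for everything: "All statistical tests will be two-tailed", at 0.05. It then says that where treatment and control differ with p < 0.05, "the results will be interpreted as evidence of treatment effect". No outcome is named in that rule. Two paragraphs later, after the CPD regression, it adds: "Analyses of secondary outcomes will be similar to the analysis of the primary outcome".

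Section {27b} multiplies the tests: "Primary and secondary outcomes will be analyzed separately within each of the three groups". The sample size section {19} describes the structure as follows: "We will conduct three separate trials, each targeting a specific group of people who smoke".

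The secondary outcomes appear in three places that do not match:

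- The administrative table lists six key secondaries: "Use of other tobacco products; Use of nicotine replacement therapy; Perceived risks of smoking VLNCs; Quit intention; Nicotine dependence; Forgoing cigarette behaviors".
- The Hypotheses section states six directional secondary hypotheses: non-study cigarette use, dependence, forgoing cigarettes, perceived risk, self-efficacy to quit, and intention to quit or cut down. The third aim, for example, opens: "We hypothesize that exposure to messages in combination with VLNC use will lead to (1) increased perceived risk of smoking VLNCs".
- The secondary outcomes section {16} splits other products into combusted and non-combusted, and also covers cessation medication, self-efficacy, the cigarette evaluation and expired CO.

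The protocol article does not make any secondary claim depend on the CPD result, and it does not mark any secondary outcome as supportive or exploratory.

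**The concern.** Testing secondary outcomes at a nominal 0.05 is ordinary practice. The difficulty is the interpretive sentence attached to it, which gives a secondary p-value the same reading as the primary one. Section {19} also presents power for secondary outcomes, and the Hypotheses section gives six of them a predicted direction, so a reader has no textual reason to treat them as lesser evidence.

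Suppose CPD shows no difference in any population and one secondary outcome reaches p < 0.05 in one population. The plan's own wording would let that be reported as evidence of a treatment effect on that outcome, although such a result is not unusual when nothing is going on. The abstract says the results will inform FDA regulatory strategies, so the status of such a finding should be settled before the data are seen.

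**Working it through.** **Inputs from the protocol article**

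- Two-sided 0.05 per test, and p < 0.05 read as an effect: section {27a}.
- Three populations, each analysed separately: sections {19} and {27b}.
- No participant is counted twice: "each participant contributes only to the analysis group corresponding to the population in which they were enrolled" ({27b}). Test results from different populations can therefore be treated as independent.
- Number of secondary outcomes, k = 6: the length of both the key secondary list and the list of secondary hypotheses.
- k = about 10: other combusted products, non-combusted products, cessation medication, perceived risk, self-efficacy, dependence, forgoing, quit intention, cigarette evaluation and CO. This is a count from section {16}; the protocol gives no total. Counting non-study cigarettes separately makes 11.

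**Assumptions**

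- No secondary outcome has a true effect in any population.
- The correlation between outcomes, ρ, is not given. A common value for all pairs is assumed, over the range 0 to 0.8.

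**Formulas**

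The protocol states no familywise error rate, so there is none to reproduce; with k = 1 the formula returns its per-test 0.05.

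For independent outcomes, the chance of at least one p < 0.05 in one trial is F = 1 − 0.95^k.

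For correlated outcomes, with c = 1.96, F = 1 − ∫ φ(g) [Φ((c − √ρ·g)/√(1−ρ)) − Φ((−c − √ρ·g)/√(1−ρ))]^k dg, evaluated numerically.

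Over three independent populations, the chance is 1 − (1 − F)³.

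**Results**

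| k per trial | ρ | One trial | Three populations pooled |
|---|---|---|---|
| 6 | 0 | 1 − 0.95^6 = 0.265 | 1 − 0.95^18 = 0.603 |
| 6 | 0.5 | 0.207 | 0.502 |
| 6 | 0.8 | 0.139 | 0.361 |
| 10 | 0 | 1 − 0.95^10 = 0.401 | 1 − 0.95^30 = 0.785 |
| 10 | 0.5 | 0.287 | 0.637 |
| 10 | 0.8 | 0.173 | 0.434 |

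The expected number of false positives does not depend on ρ: 18 × 0.05 = 0.9 for six outcomes per trial, and 30 × 0.05 = 1.5 for ten.

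**What formal control would cost**

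Holm's procedure over six outcomes starts at 0.05/6 = 0.0083, for which the normal quantile is 2.638. At 80% power, the detectable effect at that first step grows by (2.638 + 0.842)/(1.960 + 0.842) = 1.24. The weekly-visit range stated in section {19}, d = 0.27 to 0.38, would become about 0.34 to 0.47.

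**The two six-item lists**

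They share four outcomes: perceived risk, quit intention, dependence and forgoing. The key secondary list alone has other tobacco products and nicotine replacement therapy. The hypotheses alone have non-study cigarettes and self-efficacy. The family over which error might be controlled is therefore not settled.

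**The case against.** The strongest reply is that much of this is an absence. A condensed article commonly leaves multiplicity to the analysis plan, which is not shown, and the lack of an adjustment procedure is no error in itself. That stands. What remains is a sentence the article does contain: it reads any p < 0.05 as evidence of an effect and sets no limit to the primary outcome. If the analysis plan treats secondaries differently, it conflicts with this sentence.

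A reader might infer from the pooled figures that a false secondary claim is about as likely as not. The documents do not support that as a general statement. It needs no true effect on any secondary outcome, a middling assumed correlation, and pooling over what section {19} calls separate trials in different people. Separate trials do not ordinarily share one error family, and within a single trial the chance stays below even odds throughout the range shown.

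A reader might also infer that the outcomes are wholly unranked, or that a secondary result may stand in for a null CPD result. Neither follows. One primary outcome is named consistently, a key secondary list exists, and some outcomes carry no hypothesis. The primary objective is tied to CPD alone. A significant perceived-risk result would be evidence about perceived risk, which belongs to a separate stated aim.

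Finally, making secondary tests conditional on CPD would block formal testing of the third aim whenever CPD does not differ. Controlling only the hypothesised outcomes would leave out two outcomes on the key secondary list. Both points stand, and they count against prescribing a formal hierarchy as the default.

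**Conclusion.** The point holds in a limited form. Section {27a} gives every secondary p < 0.05, in each of three populations, the same reading as the primary result. If no secondary outcome is truly affected, the chance of at least one false claim within one trial is about 0.14 to 0.27 for six outcomes and 0.17 to 0.40 for about ten, against 0.05 for a single test. Pooled over the three populations it is about 0.36 to 0.60 and 0.43 to 0.79; that is the weaker basis, given the separate-trials design. The figures rest on the count of outcomes and on an assumed common correlation between 0.8 and 0. True effects on some outcomes would lower the chance of a false claim. The CPD analysis in each trial is not affected. This is a change that should be made, not a flaw that threatens the trial.

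**What to change.** In section {27a}, limit the sentence that reads p < 0.05 as evidence of a treatment effect to CPD in each trial. Add that secondary outcomes are reported as estimates with 95% confidence intervals, not adjusted for multiplicity, as supportive or exploratory results, with no claim of effect from p < 0.05 alone.

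If the sponsor wants confirmatory claims for secondary outcomes, two steps come first: reconcile the key secondary list with the hypotheses so that one family is fixed, then control error over that family within each trial. The price is the loss of power shown above.

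The default change takes a sentence or two and alters no data, procedure or sample size. Data collection is expected to run to January 2029, so it can be made well before the final analysis. The downside is that isolated nominally significant secondary results can no longer be presented as confirmed effects.
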